### Statistical analysis

Statistical analysis will be performed using SPSS® version 21.0; SPSS Inc. Chicago, IL [28]. Data will be described using descriptive statistics, i.e., means, medians and relative frequencies (i.e., outcome per number of days of hospitalization).

As this is an exploratory study with no previous studies having been conducted, we defined 20 patients as enough to conclude on the primary outcome on feasibility. This is a compromise between the capability to respond to a specific question and a realistic perspective of recruitment capacity using just one nursing home [29].

As our primary outcome, we will measure patients’ adherence to the risk prompts through the number of times and reasons they remove the risk prompts or refuse to use prompts during the period of the study and/or withdrawing from the study.

The secondary outcomes will be the following:Patients’ satisfaction with the risk prompt displays measured on a 7-point Likert scale and open-ended questions.Healthcare professionals’ satisfaction with the risk prompt displays as measured on a 7-point Likert scale and open-ended questions regarding the overall benefits of using the displays and overall perception of its impact on decreasing risk.Historical comparison of medical and nursing charts data on the relative frequency of number of events per number of days of hospitalization registered during the period of the study, with the same period the year before.Type and frequency of adverse events recorded during the period of the study.

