The aim of this study is to develop and evaluate the feasibility of a set of risk prompt displays to communicate the risk of falls, dehydration, and pulmonary aspiration and to reflect on tailored interventions that would appropriately manage these events in nursing homes. In order to do this, a national, single-center, feasibility study will be conducted. The duration of the study for each participant will be a minimum of 3 months.

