### Eligibility criteria

All patients from the CNS residential unit (*n* = 78) who fulfil the following inclusion criteria will be invited to participate:Men or women residing at the CNS nursing home for long-term care;Risk of falling and/or dysphagia and/or dehydration defined by brief screening assessment;Willing to participate in the study;Willing to provide written informed consent;Willing to comply with the monthly required interviews.

Exclusion criteria include the presence of significant active psychiatric problems (e.g., hallucinations, confusion, psychosis) that, according to the clinical judgement of the CNS multidisciplinary team, could be aggravated with the use of risk reminders.

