#### Data collection of events

For all CNS residents, we will also collect historical data related to falls, dehydration, and pulmonary aspiration events retrospectively from medical and nursing charts within the period of the study and for the same period the year before.

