## Discussion

Thoughtful selection of proper risk prompt displays in nursing homes is an essential step along a path toward efficient communication of risks among teams. We expect that the displays will potentially improve communication given their simplicity, discretion, low complexity, and minimal physical requirements.

The results of the study will enable the planning, at a later stage, of clinical studies designed to respond to more pragmatic questions regarding the use of risk prompt displays, such as (1) efficacy of the use of the risk prompt displays, (2) better clinical trial design to evaluate the efficacy of displays, including outcomes, (3) a better treatment strategy including the combination of non-pharmacological therapies with the use of the risk prompt displays, and 4) introduction of the use of a risk prompt bracelet in the therapeutic areas studied.

A limitation of this study is that the teaching session or the monthly reports encourage event registration, resulting in an apparent increase of events during the period of the study. For that reason, we will widen data collection to all CNS residents, and will also collect data of events in the same period, 1 year before.

This study will only be conducted in one nursing home, which could be a limitation. However, the CNS population is representative in age, heterogeneity of diagnosis, and symptoms of other nursing homes. As this is a protocol for a first exploratory study, we anticipate that running the study in just one nursing home will not compromise the capability to conclude on patients’ adherence.

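### The year-on-year event comparison is defined only as events per day of stay, with no measure of uncertainty or of variation between residents, so a few residents with repeated events can move it

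*Protocol article*

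**What the plan says.** Under Secondary outcomes, the protocol article lists efficacy of the prompts in reducing the number of the three event types. The third secondary bullet under Statistical analysis makes this operational as the "relative frequency of number of events per number of days of hospitalization", comparing the study period with the same period one year before.

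The general description of methods in that section reads: "Data will be described using descriptive statistics, i.e., means, medians and relative frequencies (i.e., outcome per number of days of hospitalization". No spread, interval or rule for repeat events is named for the comparison, and the unit (resident or home) is not stated.

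The data come from the whole home: "For all CNS residents, we will also collect historical data related to falls, dehydration, and pulmonary aspiration events retrospectively from medical and nursing charts", for both periods. Eligibility criteria gives the size of the residential unit as 78. Diary records has every event noted at each nursing shift, and nothing limits the count to a resident's first event. The sample size argument covers feasibility only: "we defined 20 patients as enough to conclude on the primary outcome on feasibility".

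**The concern.** A count of events divided by days of stay treats ten falls by one resident like one fall by each of ten residents. If a frequent faller arrives, leaves, dies or becomes immobile between the two years, the home's rate changes although nothing has changed for anyone else. A reader given two bare rates cannot tell this from an effect of the prompts, or from its absence.

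The Discussion also says the results will help to plan later studies, including "better clinical trial design to evaluate the efficacy of displays, including outcomes". Choosing and sizing an event outcome for such a study would call on the proportion of residents affected and the variation between residents. A single rate per day provides neither.

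**Working it through.** There is no planned figure to reproduce. The 20 patients are a pragmatic choice without a rate, margin or power, and no number is attached to the event comparison. The check therefore asks how far the rate can move by chance.

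**Inputs from the article.** 78 residents; follow-up: "The duration of the study for each participant will be a minimum of 3 months", taken as 90 days, so 78 × 90 = 7,020 resident-days per period.

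**Assumed inputs.** A mean of 0.5 events per resident per period, so 78 × 0.5 = 39 expected events; equal resident-days in both periods; counts either Poisson or negative binomial with dispersion k = 1, 0.5 or 0.25. Overlap, the share of residents present in both years with unchanged risk, is varied from 0 to 100%.

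**How one resident acts on the rate (illustrative counts).** Year before: 29 / 7,020 = 4.13 per 1,000 days. Study period: 20 / 7,020 = 2.85 per 1,000 days, an apparent reduction. Add 12 events in a single resident: 32 / 7,020 = 4.56 per 1,000 days, an apparent increase.

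**Approximation by hand, no overlap, no true change.** The variance of a period total is inflated by V = 1 + 0.5/k, giving V = 1 (Poisson), 1.5, 2 and 3. The standard deviation of the log rate ratio is √(2V/39) = 0.226, 0.277, 0.320 and 0.392. A shift of 30% or more means a ratio of at most 0.70 or at least 1.43, that is |log ratio| ≥ 0.357. The standardised distances are 1.58, 1.29, 1.11 and 0.91, with two-sided probabilities of about 12%, 20%, 27% and 36%.

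**Simulation (40,000 pairs of periods, no true change).** Probability that the crude rate shifts by 30% or more:

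| Dispersion | No overlap | 50% overlap | 75% overlap | Full overlap, stable risk |
|---|---|---|---|---|
| Poisson | 12% | 12% | 12% | 13% |
| k = 1 | 21% | 17% | 15% | 13% |
| k = 0.5 | 27% | 21% | 17% | 13% |
| k = 0.25 | 37% | 27% | 21% | 13% |

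At a mean of 1.0 events, the no-overlap figures are about 3% (Poisson) and 12–33% (clustered). With full overlap they stay at about 3%.

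**Would an ordinary interval do?** A nominal 95% interval that treats each event as independent excludes a ratio of 1 when 1.96/√V is exceeded. For V = 1.5 this is 1.60 (about 11%), and for V = 3 it is 1.13 (about 26%). Simulation gave 11–25% across the clustered cases with no overlap, against a nominal 5%.

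**Is the proportion of residents affected a better arbiter of direction?** Suppose a true rate ratio of 0.70, a mean of 0.5 and no overlap. The rate shows no reduction or an increase in 13–20% of clustered runs, and the proportion with at least one event does so in 18–29%. The proportion responds less: a rate ratio of 0.70 moves it only by a ratio of 0.75 (Poisson) to 0.82 (k = 0.25).

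**The case against.** The strongest reply is that much of this is detail that a condensed article leaves to an analysis plan. Events per day of stay is a legitimate measure: it counts repeats, adjusts for exposure and matches an aim framed as reducing the number of events. That stands, and it is a main reason why the point is minor. What remains is that the article does fix the metric for this comparison and fixes it without uncertainty.

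Four stronger readings are tempting, and the documents do not support them.

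- A reader might infer that all events are pooled into one rate and that no resident-level figure can survive. Pooling is the natural reading, but the article never states the unit. It names means and medians, which could be taken over residents, and it codes participants individually. Resident-level figures are not committed to, but they can be derived.
- A reader might take 21–37% as the expected instability. Those figures need clustered events and no resident in common. The home takes long-term residents, so some overlap is likely, but it also has short admissions, and no turnover figure is given.
- A reader might infer that the proportion of residents affected is the safer measure because it moves by 30% less often. It varies less partly because it responds less, and it misses the direction of a true 30% reduction more often than the rate.
- A reader might conclude that one or two residents usually decide the direction. Under a true 30% reduction, with 20 or 78 residents and assumed rates of 0.5 to 3.0 events per resident-year, dropping the top 5% of residents from both periods reversed the direction in only 0.1–8% of runs. With few events, much of the instability is plain Poisson noise.

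**Conclusion.** The point holds in limited form. The comparison serving the efficacy outcome is stated only as events per day of stay, without any measure of uncertainty or of variation between residents, and turnover or changing risk in a few residents with repeated events can move it materially.

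The size is conditional on an assumed mean of 0.5 events per resident, 78 residents and no true change. A shift of 30% or more then occurs in about 12–13% of comparisons from Poisson noise alone or under full overlap with stable risk, and in up to 21–37% with clustering and no overlap. The article gives nothing that would place the home within that range.

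Severity is minor. The outcome is secondary and descriptive, no test or interval is planned that this would invalidate, and the primary feasibility outcome is untouched.

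**What to change.** In the third secondary bullet under Statistical analysis:

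1. State that the rate is total events divided by total resident-days.
2. For each event type and each period, report beside it the number and percentage of residents with at least one event, and the distribution of events per resident.
3. Give the rate ratio with an interval obtained by resampling residents, not events. For a resident present in both years, keep the two periods together in the resampling; treating them as unrelated would overstate the variance.
4. Interpret the comparison through that interval. Do not adopt a rule that describes a direction only when the rate and the proportion agree, since the less sensitive proportion would then suppress true changes.

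The chart data already planned should suffice. The cost is a little more analysis, and an interval that may show the comparison to be inconclusive.

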### Data record

Study documents will be archived at the CNS in a way to ensure (1) their integrity once placed within the archive, (2) to prevent unauthorized access, and (3) to guarantee that they are readily available, upon request, by the competent authorities. The information will be confidentially handled in order to prevent subject names or other directly identifiable information appearing in any reports, publications, or other disclosures of clinical study outcomes. The investigator will assign a code to each participant and save personal information (name, birth, contacts) in a different database from the one in which statistical analysis will be performed.

## Discussion

Thoughtful selection of proper risk prompt displays in nursing homes is an essential step along a path toward efficient communication of risks among teams. We expect that the displays will potentially improve communication given their simplicity, discretion, low complexity, and minimal physical requirements.

The results of the study will enable the planning, at a later stage, of clinical studies designed to respond to more pragmatic questions regarding the use of risk prompt displays, such as (1) efficacy of the use of the risk prompt displays, (2) better clinical trial design to evaluate the efficacy of displays, including outcomes, (3) a better treatment strategy including the combination of non-pharmacological therapies with the use of the risk prompt displays, and 4) introduction of the use of a risk prompt bracelet in the therapeutic areas studied.

A limitation of this study is that the teaching session or the monthly reports encourage event registration, resulting in an apparent increase of events during the period of the study. For that reason, we will widen data collection to all CNS residents, and will also collect data of events in the same period, 1 year before.

This study will only be conducted in one nursing home, which could be a limitation. However, the CNS population is representative in age, heterogeneity of diagnosis, and symptoms of other nursing homes. As this is a protocol for a first exploratory study, we anticipate that running the study in just one nursing home will not compromise the capability to conclude on patients’ adherence.

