**Methods/Design:**

All patients from Campus Neurológico Sénior (CNS) nursing home, at risk of falls and/ordysphagia and/or dehydration will be invited to participate in the study. Patients will undertake a screeningrisk assessment and the corresponding risk prompts will be attributed. Study duration will be a minimum ofthree months per participant, including daily record of falls, dehydration and pulmonary aspiration eventsand monthly interview assessments, conducted by a member of the research team. Data of the events that occur will be compared with historical data extracted retrospectively from medical and nursing charts. This study has been approved by the Ethics Committee of the Medical Academic Center of Lisbon, Faculty of Medicine, University of Lisbon (Ref. 176/15). All participants will give their written informed consent before entering the study.

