#### Monthly reports

At the end of each month, as a strategy to keep healthcare professionals informed and to ensure they remember the importance of registering events, a newsletter will be sent to all CNS staff. This will contain information about the study duration and will present a summary of the number of participants in the study (number of patients recruited and number of drop-outs) and of the falls, dehydration, and pulmonary aspiration events recorded in that month.

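### Collecting all residents' data and prior-year data does not remove the over-registration the protocol expects, so the before/after event rate cannot be read as efficacy

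*Protocol article*

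**What the plan says.** The Discussion names a limitation: the teaching session or the monthly reports may prompt staff to record more, so that events seem to rise during the study. The remedy follows directly: "we will widen data collection to all CNS residents, and will also collect data of events in the same period, 1 year before".

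Data collection of events repeats the plan. For all residents, events are taken from medical and nursing charts "within the period of the study and for the same period the year before". Statistical analysis gives the only event comparison: "Historical comparison of medical and nursing charts data on the relative frequency of number of events per number of days of hospitalization", study period against the same period a year earlier. It does not name the population for this comparison, and no contrast of participants with non-participants appears anywhere in the article. Secondary outcomes assigns the event counts an efficacy purpose, namely whether the displays reduce falls, aspiration and dehydration.

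On who receives the recording stimulus, the Preparation phase describes training for the multidisciplinary team, and Monthly reports says that "a newsletter will be sent to all CNS staff".

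**The concern.** The Discussion presents two data-collection steps as the answer to a bias that it has itself identified. A bias that acts only in the later period cannot be removed by comparing that period with an earlier one, because that comparison is where the bias enters. Adding residents whose charts are kept by the same trained and reminded staff does not help either, unless those residents serve as a concurrent comparison. The article does not say that they will.

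A real reduction in events could therefore look smaller than it is, vanish, or appear as an increase, while the reader is told that the problem has been addressed. The article says that its results will feed the planning of later efficacy studies, so a misleading event signal would be carried forward.

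**Working it through.** The article's sample size of 20 rests on judgement and recruitment capacity, so there is no calculation of its own to reproduce.

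**Inputs from the article**
- Residents in the unit: 78 (Eligibility criteria).
- Target enrolment: 20 (Statistical analysis: "we defined 20 patients as enough to conclude on the primary outcome on feasibility"). No cap is stated, and all eligible residents are invited.
- Participants are selected for risk (Eligibility criteria: "Risk of falling and/or dysphagia and/or dehydration defined by brief screening assessment"), so their event rate is probably above that of other residents.
- Over-registration: direction stated, size not given.

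**Assumptions (not in the article)**
- r = relative over-registration in the study period.
- e = true relative reduction in participants; 30% is used for illustration.
- k = event rate of participants divided by that of other residents; range 1 to 3.

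**Step 1: does the remedy remove the bias?** With no true effect (e = 0), the before/after ratio is 1 + r in participants and 1 + r in all residents. At r = 20% both read 1.20. Neither step changes this.

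**Step 2: what pooling would add.** Participants' share of baseline events is f = nk / (nk + 78 − n), and the pooled ratio is (1 + r)(1 − f·e). It exceeds 1 when r > 1/(1 − f·e) − 1. For n = 20 and e = 30%:

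| k | f | Ratio at r = 0 | Break-even r | Ratio at r = 20% |
|---|---|---|---|---|
| 1 | 20/78 = 0.256 | 0.923 | 8.3% | 1.11 |
| 2 | 40/98 = 0.408 | 0.878 | 14.0% | 1.05 |
| 3 | 60/118 = 0.508 | 0.847 | 18.0% | 1.02 |

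Dilution lessens if more residents enrol: with k = 1, f = 40/78 = 0.51 at n = 40 and 60/78 = 0.77 at n = 60.

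**Step 3: participants only.** The ratio is (1 + r)(1 − e). At r = 20% and e = 30% it is 1.20 × 0.70 = 0.84. The sign reverses only above 1/0.70 − 1 = 42.9%. The ratio is still biased, but there is no dilution.

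**Step 4: participants against non-participants.** If r is the same in both groups, [(1 + r)(1 − e)] / (1 + r) = 1 − e = 0.70, whatever r is.

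**Step 5: precision.** Assume 6 falls per 1000 days, 90 days, 20 participants and 58 others. Expected falls per period are 20 × 90 × 0.006 = 10.8 and 58 × 90 × 0.006 = 31.3. Poisson 95% interval factors:
- participants before/after: exp(1.96 × √(2/10.8)) = 2.32
- ratio of the two ratios: exp(1.96 × √(2/10.8 + 2/31.3)) = 2.66

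**The case against.** The strongest reply is that the article fixes which data are collected, not how they are pooled. Collecting non-participants' events in both periods is compatible with using them as a reference for drift in recording, and an analysis plan that is not shown could say so. This stands as far as pooling is concerned. A reader might infer that the plan will cut the prompt effect to a quarter. The article does not support that as a statement of fact: it needs a pooled analysis, exactly 20 of 78 enrolled, and equal event rates in a group chosen for risk. It does not rescue the Discussion, which presents the two collection steps as the answer, while the one comparison that is defined is before/after.

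A reader might also infer a conflict of sources from the abstract: "Data of the events that occur will be compared with historical data extracted retrospectively from medical and nursing charts". That sentence follows a mention of daily records, but Data collection of events and Statistical analysis both specify charts for the two periods. This is loose wording in the abstract, and chart extraction gives some separation from the study's own shift forms.

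The proposed contrast has real weaknesses. Recording may rise more for participants. Trained care may spill over to others. Participants are chosen for current risk, while non-participants include low-risk residents, people who decline, and those excluded on psychiatric grounds. No earlier length of stay is required, so some participants may have no prior-year data. The estimate is also imprecise: 0.70 with a factor of 2.66 spans about 0.26 to 1.86. These points mean the result must be labelled exploratory. They do not make the unadjusted before/after ratio a better choice.

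**Conclusion.** The concern holds in a limited form. The remedy in the Discussion leaves the acknowledged inflation fully in place, at 1 + r, for participants and for all residents alike. This needs only that the recording stimulus acts in the study period and not the year before. That extending the data to all residents brings no relief follows from the stimulus reaching all staff.

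Dilution and sign reversal are conditional. If all residents are pooled with 20 enrolled, 26% to 51% of the effect survives for k from 1 to 3. A true 30% reduction then shows as an increase once over-registration passes about 8% to 18%. The values of r, e and k are assumptions, because the article gives none.

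This should be fixed, but it does not threaten the study's main conclusion, as a reader might infer. The comparison is a descriptive secondary outcome in a feasibility study, no test or decision rule depends on it, the expected rise is disclosed, and efficacy is deferred to later work.

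**What to change.** In Statistical analysis, state that, using chart-extracted events:
1. The rate ratio of the study period to the prior year is reported separately for participants and for long-term non-participants. Short-stay residents are left out because they are not eligible.
2. Participants' study-period events and days are counted from the day the prompts are placed.
3. The participants' ratio divided by the non-participants' ratio, with its interval, is the exploratory estimate of the prompt effect.
4. Neither the unadjusted participant ratio nor any pooled all-resident ratio is read as efficacy.
5. A rule is given for residents with no prior-year data.

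In the Discussion, replace the present rationale: the all-resident data help because non-participants show the change in recording that is common to both groups, and the prior year alone does not correct for it.

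The cost is mostly wording, since chart data for all residents in both periods are already planned. Prompt placement dates and participant status must be linked to the chart extraction. The downsides to state are an interval factor of about 2.7 instead of 2.3 under the assumed fall rate (wider with repeat fallers), removal of over-registration only where it is common to both groups, spill-over of trained care, selection of participants for risk, and incomplete prior-year data. If the sponsor finds these limits too severe, the alternative is to report the event rates descriptively and drop the efficacy reading.
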